## 6.16 questionnaire translation, validity and reliability

**Quantitative data**: An essential step for the questionnaire's validity is the translation of the original English version into a native language (Wild et al., 2005). We'll follow a methodical procedure suggested by Beaton et al. (Dorcas E. Beaton, 2000) to maintain conceptual, experiential, and idiomatic equivalence. Bilingual translators will translate the instruments into Hadiyisa. The instruments will be translated back into English by two bilingual translators from the Department of Hadiyisa, Wachemo University, who are completely blind to the original English version. To establish semantic equivalence, the back-translation is necessary. To combine all language versions and create the pre-final questionnaire for field testing, an expert committee meeting will be organized (Abdulahi et al., 2018). To verify the translation's accuracy, the original and back-translated English versions of the instruments will be compared. Using a technique developed by Skperber et al. (Sperber et al., 2016), each item in the original and back-translated versions will be ranked in terms of comparability of language and similarity of interpretability for the purpose of certifying the translated instrument. Fluent in English experts from the department of foreign languages and literatures will assess the comparisons using Likert scales from 1 (highly comparable/extremely similar) to 7 (not at all comparable/not at all similar). There will be a formal evaluation of the translation for any mean score greater than 3.

Pilot testing of the translated tool will be conducted among 27 couples who will not be included in the actual trial to assess its understanding, comprehension, and appropriateness. Additionally, subject experts will evaluate the content, and the necessary changes will be made (Figure 8). The tools' internal consistency will be tested using Cronbach's alpha. A tool with a Crombach alpha of ≥ 0.7 will be considered reliable(Sharma, 2016). Finally, the questionnaires will be utilized at the study's baseline and completion.

Content Validity

(IPVp)

Forward translation by public health experts /group-1

Forward translation by Language experts/group-2

Backward translation by

Public health experts/group-3

Backward translation by language experts /group 4

Review of 4 version of the questionnaire and final versison (IPVp)

Determine face validity of the pre-final version (IPVp) and revise the questionnaire if necessary

Conduct a pre-test study on the pre-final version (IPVp) and revise the questionnaire if necessary

Final-version (IPVp)-field work

Figure 7:Schematic representation of validation process of the questionnaire (IPVp)

**6.17 outcomes of interest and measurement**

**Dependent variables:** experience of intimate partner violence (IPV) in the form of physical, psychological, or sexual violence from the male partner is an independent variable of the study among couples.

**Physical intimate partner violence**: During data collection, pregnant women will be asked six physical intimate partner violence questions: (i) “Slap or throw something at her that could hurt her”, (ii) “Pushed shoved her or pulled her hair”, (iii) “Hit her with his fist or with something else that could hurt her”, and (iv) "Kicked, dragged, or beaten her up." (v) “Attempted to choke or burn her on purpose” and (vi) "threatened to use or actually use a gun, knife, or other weapon against her” (Abramsky et al., 2011) in the last 12 months and during the most recent pregnancy. If the mother responds to one or more of these, dichotomous dependent variables will be created from these questions.

If a pregnant mother answers one or more of these physical intimate partner violence questions, 1=yes (experienced physical intimate partner violence), and otherwise, 0=not experienced physical intimate partner violence.

**Sexual intimate partner violence**: A pregnant woman will be asked for three sexual intimate partner violence questions: whether her husband (i) physically forced her to have sexual intercourse with him when she did not want to”, (ii) “forced her with threats or in any other way to perform sexual acts she did not want,” and (iii) "physically forced to perform any other sexual acts she did not want to” (Abramsky et al., 2011) in the last 12 months and during the most recent pregnancy. If the pregnant mother answers one or more of these sexual intimate partner violence questions, 1=yes (experienced sexual intimate partner violence), and otherwise, 0=no (not experienced any sexual intimate partner violence since the start of this pregnancy).

**Emotional/psychological violence: a** pregnant mother will be asked the following three psychological violence questions: (i) “say or do something to humiliate her in front of another person”, (ii) "threat to hurt or harm her or someone she cares about,” and (iii) insult or make her feel bad about herself” in the last 12 months and during the most recent pregnancy (Abramsky et al., 2011). If the mother responds to one of these emotional or psychological IPV questions, it will be recorded as 1 = yes; otherwise, 0=no (she has not experienced any emotional or psychological intimate partner violence during this pregnancy).

**Social support: The** Oslo-3 Social Support Scale (OSSS-3) will be used to measure the social support of women. The OSSS-3 consists of three items assessing the level of social support among women. Pregnant women will be asked, **Oslo 1**: How many people are so close to you that you can count on them if you have great personal problems? The responses will be: 1. 'None, 2. ‘1–2’ 3. ‘3–5’ 4, ‘5+’; **Oslo 2:** How much interest and concern do people show in what you do? The responses will be "none."2 ‘little’ 3 ‘uncertain’ 4 ‘some’ 5 ‘a lot’ and **Oslo 3**: How easy is it to get practical help from neighbors if you should need it? The response will be 'very difficult. 2 ‘difficult’ 3 ‘possible’ 4 ‘easy’ 5'very easy. The sum scores range from 3 to 14. Then the sum scores will be categorized as 3–8 (**poor social support**), 9–11 (moderate**social support),** and 12–14 (strong**social support**).

**Knowledge of IPV:** couples will be asked about nine items of knowledge questions on IPV. Couples who scored about 75% or above of the correct answer will be scored as “good knowledge,” and those who scored less than 75% will be scored as “poor knowledge (Oche et al., 2020).

**Attitude towards IPV**: To measure attitude toward intimate partner violence during pregnancy, couples will be asked, “In your opinion, is a husband justified in hitting or beating his wife in the following situations?" (a) “If she goes out without telling him?” (b) “If she neglects the children?” (c) “If she argues with him?” (d) “If she refuses to have sex with him?” (e) “If she burns the food?” Responses of “supportive attitude toward IPVp” to one or more of the scenarios were coded 1; “not supportive attitude toward IPVp" to all scenarios was coded '0'. (Trott et al., 2017).

**Controlling behavior**: couples will be asked six questions: (i) “jealous if she talked with other men”, (ii) ”accused her of unfaithfulness”, (iii) “did not permit her to meet her friends,(iv) “tried to limit her contact with family,(v) “insisted on knowing where she is, and “did not trust her with money(Antai, 2011). Couples responded “yes” to one or more of the control questions coded as 1. Otherwise, it will be coded 'no as 0.

**Women’s autonomy**: women's decision-making Autonomy will be assessed by asking couples who decide on household purchases, including small and large ones, and who decides on visiting relatives and friends. Who decides how to spend the wife's earnings? Who decides the number of children to have? And who decides to obtain health care for themselves? The response options will be “husband only’’, wife only’’ or ‘’both husband and wife”. Women will be considered to participate in decision-making if they make decisions alone or jointly with their husbands. A composite measure will be created using the sums of equally weighted binary input variables. Women will be scored one (1) for answers to each variable that included her (alone or jointly) in decision-making; otherwise, they will be scored zero (0). The index of household decision-making power (autonomy) contains five variables; thus, the respondents will be scored from 0 to 5. Two binary measures from these indexes will be created to indicate women with higher versus lower autonomy. The high and low categories will be created by dividing the sample indexes into approximately half, in which those who score below the mean score are considered to have low autonomy or lower involvement in household decision-making, and those who score above the mean score are considered to have higher decision-making autonomy or higher involvement in household decision-making (Uthman et al., 2009).

**Women’s Self-Efficacy: The** Generalized Self-Efficacy Scale (GSES), which was developed by Albert Bandura, will be used. The General Self-Efficiency Scale (GSES) consists of 10 items scored on a 4-point Likert scale, from 1 (not at all true) to 4 (exactly true). The total scale ranges from 10 to 40, with higher self-efficacy (score of ≥20) and lower self-efficacy (score of <20) (Liping Peng et al., 2020).

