**6.8 sample size**

**Qualitative study:** the sample size for a qualitative study will be determined by information saturation (Dworkin, 2012). But, for planning purposes, eight (8) Focus Group Discussions (FDG)( at least two FGDs from male partners (husbands of pregnant women), two FGDs from religious leaders, two FGDs from community leaders, and two FGDs from the women's development army) will be considered. Moreover, six in-depth interviews (IDI) among pregnant women and 70**participants** will be involved in FGD, and IDI will be involved in order to explore community perspectives towards IPV in pregnancy.

**Quantitative study (CRCT):** sample size is calculated by using the following parameters: The prevalence of IPV during pregnancy (p) was  37.5% in a study conducted in Tigray, Ethiopia (Adhena et al., 2020). The expected decline of IPVp following the intervention will be 20%, with 80% power, a 95% confidence interval, an intra-correlation coefficient (ICC) variation of 0.05, a loss to follow-up of 20%, and a design effect of 2.3. Hence, the sample size is based on Stata version 16.

Design Effect (DE) = 1 + ρ (m-1)

Where,

DE=Design effect,

ρ= intra-cluster correlation coefficient = 0.05

m=number of participants per cluster = 27.

DE=1+0.05(27-1) =2.3

Attrition (20%)

=216 couples per control group and 216 couples per intervention group; sample size =432 couples, making a total of 864 participants.

Total cluster (k) = 16 kebeles (clusters)

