**6.15.2 Description of education sessions**

**Control group (study group 1):** participants in the control clusters receive routine standard care from the health extension workers**.** Education on violence prevention, including intimate partner violence, will not be provided by the research team. This group will simply receive the health extension package services provided by HEWs.

**Intervention group (study group 2)**: Pregnant women and their husbands will receive couple-based violence prevention education (CBVPE) from the 13–16 weeks of gestation to delivery for six months. The intervention package is aimed at raising knowledge and awareness of gender-based violence, types of intimate partner violence, adverse maternal and new-born outcomes of IPV during pregnancy, common triggers of intimate partner violence during pregnancy and its management, a healthy relationship in marriage, communication, and problem-solving skills. After adequate training, HEWs will provide health education to couples in the intervention arms at the health post in groups. It will be provided every month for six consecutive times. Each session may take 50-60 minutes. All sessions will contain interactive lectures, take-home exercises, and reflection. During class sessions, flip chart paper and posters will be used. It is designed with the intention that they will be carried out in an enclosed workshop space. Neither the HEWs nor the participants will be informed about the intervention hypothesis.

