**6.24 Data processing and analysis**

**Qualitative Data:** The complete data will be exported to ATLAS Ti. 7.0 for data analysis. The codes will be created initially by independent coders. The codes will be merged after discussion to reach consensus codes. At least two coders will be involved in the coding process and categorization of the codes. These codes will be merged into larger categories and then set into sub-themes. Sub-themes will be reviewed further to develop overarching themes**.** Then the data will be summarized and reported with some important direct quotes.

**Quantitative data:** A complete questionnaire with individual code and specific cluster will be exported from server to SPSS or STATA for analysis. At baseline, descriptive statistics such as proportions, percentages, tables, diagrams, and figures will be used to describe the study population at the intervention and control arms before the intervention starts. The baseline characteristics of the participants and their prior exposure to intimate partner violence will be examined and compared between the intervention and control groups. The chi-square test and independent sample t-test will be used to compare the baseline characteristics for categorical and continuous variables, respectively. After the end-line survey, the proportion of women who experienced intimate partner violence during the trial period will be calculated with a corresponding confidence interval.

We will use the McNemar test to appreciate the differences in outcomes of interest in both intervention and control groups before and after the intervention for categorical data. A paired t-test will be used to compare continues outcome of interest in the intervention and the control groups after and before the intervention. A model of longitudinal data analysis, the GEE (Generalized Estimating Equation), will be used to test the independent effect of the intervention on the outcome of the interest. Data analysis will be performed with an intention-to-treat analysis approach. During the analysis, the effect size, confidence interval, and p-value will be calculated. A model with the smallest Quasi-likelihood under the Independence Model Criterion (QIC) will be used to select the best-fitted model. All tests will be two-sided, and statistical significance will be declared at p < 0.05.

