| 708 | When I am confronted with a problem, I can usually find several solutions. | | | | | | 1 | | | | 2 | | | | 3 | | | | 4 |  | | |
| 709 | If I am in trouble, I can usually think of a solution | | | | | | 1 | | | | 2 | | | | 3 | | | | 4 |  | | |
| 710 | I can usually handle whatever comes my way. | | | | | | 1 | | | | 2 | | | | 3 | | | | 4 |  | | |
|  | **PART SEVEN: experience of intimate partner violence in the recent pregnancy(last pregnancy)** | | | | | | | | | | | | | | | | | | | | |  |
| 801 | **Physical** | | | | | | | | | | | | | | | | | | |  | |  |
|  | During recent pregnancy, did your partner: | Slap you or throw something at you Yes No  that could hurt you? ………………………………1 2  Push you, shove you or pull your hair……………..1 2  Hit you with his fist or with something  else that could hurt you?..........................................1 2  Kick you, drag you about or beat you up?...............1 2  Attempt to choke you or burn you on purpose?.......1 2  Threaten to use or actually use a gun,  Knife or other weapon against you? …..…………1 2 | | | | | | | | | | | | | | | | | |  | |  |
| 802 | **Psychological** | Yes No  Say or do something to humiliate  you in front of another person?....................1 2  Threaten to hurt or harm you or  someone you care about? ………………...1 2  Insult you or make you feel bad about yourself?...1 2  Do things to scare or intimidate you  on purpose (e.g., by the way he looked at you,  by yelling and smashing things)?...................1 2 | | | | | | | | | | | | | | | | | |  | |  |
|  | During your most recent pregnancy, did your partner: |  |  |  |  |  |  |  |  |  |  |  |  |  |  |  |  |  |  |  |  |  |
| 803 | **Sexual** |  | | | | | | | | | | | | | | | | | |  | |  |
|  | During your recent pregnancy, did your partner | Yes No  Physically force you to have sexual  intercourse with him when you did not want to?.....1 2  Force you with threats or in any other way  to perform sexual acts you did not want?.............1 2  Physically force you to perform any  other sexual acts you did not want to? …………....1 2 | | | | | | | | | | | | | | | | | |  | |  |
| 804 | If a woman is yes for 801 or 802 or 803, what did you do? | Nothing……………………………………………………..…..1  Reported to him relations…………………………………….....2  Quit relationship……………………………………………...…3 | | | | | | | | | | | | | | | | | | If ‘nothing’ skip to  805 | |  |

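### The primary outcome has conflicting time windows, and the only ones the questions ask about include violence from before the first education session, which dilutes the effect by an unknown amount

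*Protocol*

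**What the plan says.** The protocol gives the primary outcome, any physical, psychological or sexual violence by the partner, four different time frames.

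- **Section 6.17** asks the items "in the last 12 months and during the most recent pregnancy". One or more positive answers scores 1. The zero codes for sexual and psychological violence refer to this pregnancy. Section 6.21 repeats the two-part window.
- **Section 5.10** defines violence as occurring during pregnancy.
- **Section 6.24 (data processing and analysis)** says that at endline "the proportion of women who experienced intimate partner violence during the trial period will be calculated".
- **Annex II, Part Seven** is headed "experience of intimate partner violence in the recent pregnancy(last pregnancy" (bracket closed in the original). Its items carry no dates, and there is no 12-month item. Part Four deals separately with the current pregnancy.

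On timing, baseline is at 10–12 weeks of gestation (6.15.1). Education runs "from the 13–16 weeks of gestation to delivery for six months" (6.15.2). Endline follows after 8 months (6.2). The same questionnaires are used at both surveys (6.16).

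The item set also differs. In section 6.17 women are "asked the following three psychological violence questions", whereas item 802 of Annex II has a fourth act, beginning "Do things to scare or intimidate you".

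**The concern.** Education that starts at 13–16 weeks cannot prevent violence in the weeks before. If those weeks count, a woman whose partner stops completely after session 1 is still recorded as a case. Randomisation should balance these early cases, so they do not favour either arm. They put the same floor under both rates and shrink the difference. A null result could then mean that the education failed or that the outcome could not register its success.

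The analysis section appears to want a window limited to the trial, but no question supplies the data for it. The before-after McNemar comparison has a related problem. At baseline the recent (last) pregnancy may be understood as an earlier one, and every eligible woman has had a live birth. At a postpartum endline it is presumably the index pregnancy. Before and after could then be different quantities.

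**Working it through.** **1. Which window holds at endline.** Baseline at 10–12 weeks plus 8 months (about 35 weeks) puts endline about 45–47 weeks after the start of pregnancy. A 12-month look-back from there covers the whole pregnancy. So whether the two parts of the section 6.17 window are joined as either, both, or taken singly, the first 13–16 weeks are inside it.

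**2. The plan's own figure.** Section 6.8 gives "37.5% in a study conducted in Tigray, Ethiopia" as the control rate and says "The expected decline of IPVp following the intervention will be 20%, with 80% power, a 95% confidence interval". It does not say whether 20% is absolute or relative.
- Absolute (37.5% to 17.5%): the pooled two-proportion formula, two-sided 5%, 80% power, gives 78 per arm. 78 × 2.3 × 1.2 = 215.3, against 216 stated. The unpooled formula also fits: 75 × 2.3 / 0.8 = 215.6.
- Relative (37.5% to 30%): 623 × 2.3 × 1.2 = 1,719 per arm, which does not fit.

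The plan therefore implies 17.5%, a relative fall of 0.20/0.375 = 53%.

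**3. Effective sample size.** There are 8 kebeles per arm, with 27 × 0.8 = 21.6 women each after 20% loss, and ICC 0.05. The design effect is 1 + 0.05 × 20.6 = 2.03, so effective n = 8 × 21.6 / 2.03 = 85 per arm. Keeping the stated 2.3 gives 172.8 / 2.3 = 75.

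**4. Dilution as a function of f.** Let f be the share of control-arm cases already positive before session 1 (assumed). The floor is 0.375f. A 53% cut in later new cases gives p2 = 0.375f + 0.467 × 0.375(1 − f). Power = Φ(Δ/√{[p1(1−p1) + p2(1−p2)]/85} − 1.96), with p1 = 0.375.

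| f | Floor | p2 | Power | Cut in later cases needed to show 17.5% |
|---|---|---|---|---|
| 0 | 0% | 17.5% | 85% | 53% |
| 0.1 | 3.8% | 19.5% | 76% | 59% |
| 0.2 | 7.5% | 21.5% | 64% | 67% |
| 0.3 | 11.3% | 23.5% | 52% | 76% |
| 0.4 | 15.0% | 25.5% | 40% | 89% |
| 0.467 | 17.5% | 26.8% | 32% | 100% |

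With effective n 75, each power is about 3–6 points lower.

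**5. One anchor for f.** Assume constant risk over 40 weeks reaching 37.5%, with session 1 at week 13.
- Already cases: 1 − 0.625^(13/40) = 14.2% (f = 0.142/0.375 = 0.38).
- Later risk: 1 − 0.625^(27/40) = 27.2%. A 53% cut makes it 12.7%.
- Whole-pregnancy rate: 0.142 + 0.858 × 0.127 = 25.1%, a difference of 12.4 points; power 42%.
- With session 1 at week 16, the rate is 26.6% and power 33%.

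**6. The same true effect in a narrower window.**
- Opening at week 13 with session 1: 27.2% v 12.7%, z = 2.41, power 67%.
- Opening at week 16 with session 1: 24.6% v 11.5%, power 62%.
- Opening at baseline: power runs from 47% (baseline week 10, session 1 week 16; 29.7% v 17.5%) to 65% (baseline week 12, session 1 week 13; 28.0% v 13.7%).

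These are normal approximations. A t reference with 14 degrees of freedom lowers both sides, for example 42% to about 38% and 67% to about 61%.

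**The case against.** The strongest objection is that f is unknown. A reader might infer that 17.5% is almost unreachable. The documents do not support that: it is a fair description at f of about 0.4 or more, but at f = 0.2 a 67% cut would be enough. If violence mostly begins later in pregnancy, the loss is modest. This stands, and the result has to be given as a range.

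Second, section 6.24 names the trial period, so the plan has not settled on counting earlier violence. This also stands: the fault is a contradiction. It does not remove the problem, because no question collects the trial-period outcome.

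Third, a reader might infer that any act in the past 12 months, including before conception, makes a woman a case. The text joins the two windows with *and*, the zero codes refer to this pregnancy, and the annex has no 12-month item, so this is not established. Nor is it certain that baseline records a previous pregnancy, since those zero codes point the other way.

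Finally, narrowing the window changes what is estimated and lowers the control rate, and 37.5% is a during-pregnancy prevalence. That is a real cost. For the same true effect, power still rises.

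**Conclusion.** The concern holds as an unreconciled outcome window whose only collectable versions include time before the intervention. Dilution is present at any f above zero; only its size is assumed. Power for the planned effect falls from about 85% at f = 0 to about 40% at f = 0.4, and to 33–42% under constant risk over 40 weeks. The implied 17.5% is out of reach only when f exceeds 0.175/0.375 = 0.467. These figures rest on reading the planned decline as 20 percentage points (which reproduces the 216), ICC 0.05, 20% loss and a normal approximation. The pregnancy wording and the three-versus-four psychological items are separate inconsistencies in the same outcome. They do not enter the power figures but need settling with it.

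**What to change.** - **Endline:** ask every violence item, in both arms, for one window with a fixed start and a fixed end. It can start at the baseline interview or, with less dilution, at a common calendar or gestational date at or after the first session. A baseline start leaves 1–6 untreated weeks inside. Make any act in that window the primary outcome.
- **Baseline:** ask about the current pregnancy, and use the answer as an adjustment covariate, not as the before value in a McNemar comparison.
- **Alignment:** make sections 5.10, 6.17, 6.21 and 6.24 and Annex II Part Seven state the same window, and score the same psychological items at both surveys.
- **Sample size:** restate the control rate and power for the new window.

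**Cost.** This is more than rewording. Under constant risk the control rate falls to about 27–30% (about 25% if the window opens at week 16), and power for a 53% cut is about 47–67%, below the stated 80%. The protocol's own pooled formula with 2.3 × 1.2 gives 119 × 2.76 = 329 per arm for a window opening with session 1 at week 13, and 134 × 2.76 = 370 at week 16. This holds the design effect at 2.3, so it means more kebeles, not more couples per kebele. If 216 per arm must stand, the protocol should state the lower power. It would still exceed that of the present whole-pregnancy window on the same assumptions.

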**Knowledge and attitudes toward IPV**

Evidence recommends that IPV knowledge and attitude influence its experience or perpetration. A study in Gambia revealed that about 77.0% had good knowledge of intimate partner violence. 87 percent of subjects had a negative attitude towards IPV (Jatta and Ouedraogo, 2021). In a study done by Oche et al. (2020) in Sokoto, Northwest Nigeria, about 90.0% of participants had good knowledge of IPV (Oche et al., 2020).

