**Secondary outcome variables**

- Knowledge, attitudes, and control towards IPV during pregnancy
- Knowledge: Good versus Poor Knowledge,
- Attitude: supportive versus not supportive attitude toward IPV
- Controlling behavior: yes versus no
- Women’s autonomy and self-efficacy

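### Knowledge is analysed only as good versus poor at 75%; the 0–9 score from the same items has more power, about 1.5 to 2 times if baseline good knowledge is near 90% and less at lower baselines

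*Protocol*

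**What the plan says.** The list of secondary outcomes in section 6.6.1 gives the outcome as "Knowledge: Good versus Poor Knowledge". Section 6.17 says that "couples will be asked about nine items of knowledge questions on IPV" and sets the rule: "Couples who scored about 75% or above of the correct answer will be scored as" good knowledge, with anything lower scored as poor. It cites the study in Sokoto, Northwest Nigeria, as the source.

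The literature review, under knowledge and attitudes toward IPV, reports of that same study that "about 90.0% of participants had good knowledge of IPV". The only other level in the protocol is in the same paragraph: "A study in Gambia revealed that about 77.0% had good knowledge of intimate partner violence".

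Section 6.24 provides for continuous outcomes ("A paired t-test will be used to compare continues outcome of interest", within each arm) and plans a GEE for the intervention effect. The protocol nowhere defines knowledge as a score. It gives no baseline level for Hadiya, no expected change and no power for this outcome.

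**The concern.** Specific objective 3 asks whether the education changes couples' knowledge. The two-category outcome records a change only when a respondent crosses the line between 6 and 7 correct. Someone who goes from 7 to 9, or from 2 to 6, has learned something the analysis does not see.

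On the protocol's own evidence the line may sit low. If 77–90% are already above it at baseline, only 10–23 percentage points of improvement remain. The questionnaire points the same way. In the women's English form, items 602–609 are all statements to which yes is the knowledgeable answer, so agreeing with everything earns full marks on them.

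What is at stake is sensitivity on a named objective: a modest real gain could be missed although the data to show it are collected anyway.

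**Working it through.** **The plan's own figure first.** Section 6.8 takes control prevalence "37.5% in a study conducted in Tigray, Ethiopia", a 20% decline, 80% power, ICC 0.05, design effect 2.3 and 20% loss; section 6.24 sets a two-sided 5% level. Reading the decline as absolute (37.5% to 17.5%, mean 0.275):

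n = [1.96√(2×0.275×0.725) + 0.842√(0.375×0.625 + 0.175×0.825)]² / 0.20² = 77.05, so 78. Then 78 × 2.3 × 1.2 = 215.3, rounded up to 216 per arm. The stated size is reproduced.

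**Effective size for knowledge.** Analysed per arm: 216 × 0.8 = 172.8. With the stated design effect, 172.8 / 2.3 = 75.1. With the cluster size left after attrition (27 × 0.8 = 21.6), the design effect is 1 + 0.05 × 20.6 = 2.03 and 172.8 / 2.03 = 85.1. The ICC of 0.05 was set for IPV; using it for knowledge is an assumption.

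**The cut.** 0.75 × 9 = 6.75, so good means 7 or more of 9 (7/9 = 77.8%; 6/9 = 66.7%).

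**Power of good/poor.** Φ{[|p2−p1|√n − 1.96√(2p̄(1−p̄))] / √(p1(1−p1)+p2(1−p2))}. For 90% versus 97% at n = 75.1: (0.607 − 0.683) / 0.345 = −0.22, which is 41%.

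**Power of the score.** Φ{(μ2−μ1)/√((σ1²+σ2²)/n) − 1.96}. The score distribution is not in the documents. I assume a beta-binomial on nine items with inter-item correlation 0 to 0.3, set so that the share with 7 or more equals the assumed percentage. At correlation 0.2, 90% good gives mean 8.27 (SD 1.32) and 97% gives mean 8.75 (SD 0.80). Then 0.48 / √((1.32² + 0.80²)/75.1) = 2.70, and 2.70 − 1.96 = 0.74, which is 77%. The ratio is 0.77/0.41 = 1.9.

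At effective n 75.1 per arm:

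| % good, control vs intervention | Good/poor | 0–9 score | Ratio |
|---|---|---|---|
| 90 vs 95 | 21% | 34–50% | 1.6–2.3 |
| 90 vs 97 | 41% | 66–88% | 1.6–2.1 |
| 77 vs 90 | 57% | 77–86% | 1.3–1.5 |
| 77 vs 93 | 79% | 94–98% | 1.2 |
| 77 vs 97 | 96% | about 100% | 1.0 |
| 50 vs 65 | 46% | 59–62% | 1.3 |

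At effective n 85.1 the good/poor column reads 23%, 46%, 63%, 84%, 98% and 51%.

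**Second route.** Fix the effect so that the score has 50–90% power, with correlation 0.05–0.3. The ratio is then 1.4–2.3 at a 90% baseline, 1.2–1.65 at 77% and 1.1–1.4 at 50%. A t test on 14 degrees of freedom, for 16 clusters, barely moves these. A latent-normal model gives 2.3–2.9 at 90%, but it ignores the score's own ceiling and I do not rely on it.

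**The score's own ceiling.** At a 90% baseline the share already at 9 of 9 is 29%, 52%, 65% and 73% for correlations 0, 0.1, 0.2 and 0.3.

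**The case against.** The strongest reply is that the baseline is borrowed. Both figures come from other countries, while the trial recruits in rural kebeles. The title of the Nigerian study in the reference list ties its knowledge component to pregnant women, so it says little about husbands, who are half the respondents. Whether that study used these nine items cannot be seen. All of this stands, and it is why the ceiling can only be called possible and why the gain must be given by baseline level.

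A reader might infer that the good/poor outcome cannot show an improvement, or that a null result would reflect the cut and not the education. The documents do not support that. At effective n 85 and a 77% baseline, good/poor has about 84% power to detect 93% and 93% power to detect 95%. Six sessions that teach much of what the items ask could produce changes of that size. A null result could equally mean no effect.

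The 75% level also has a rationale within the programme. The trainer manual uses 75% of questions answered as its mastery rule in every session and repeats the session if couples fall short. That is a good reason to keep reporting the share who reach it. It does not make it the best outcome for the comparison between arms.

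The score does not cure always-yes answering, which gives full marks on either scale. The pilot in 27 couples and the planned validity testing might reveal extreme agreement, but no ceiling check is stated. Finally, the protocol claims no power for knowledge, so no stated power figure is wrong.

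**Conclusion.** The point holds as a conditional one about a secondary outcome. The protocol fixes knowledge as two categories, with a cut taken from a study it reports at about 90% good knowledge, and so discards information it collects. The 0–9 score did better in every case run, except that the advantage vanished when both analyses approached full power.

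The size depends on the unknown baseline: about 1.5 to 2 times the power near 90% good knowledge, about 1.2 to 1.6 near 77%, about 1.1 to 1.4 near 50%. Quoting 1.5 to 2 without its condition would overstate the case. At a 90% baseline roughly 30–75% may already score 9 of 9, so the score eases the ceiling without removing it.

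These figures assume ICC 0.05 for knowledge, 20% attrition, a beta-binomial score with inter-item correlation 0 to about 0.3, and baselines borrowed from the literature review. Any further gain from baseline adjustment is not counted. The primary outcome and its sample size are not affected.

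**What to change.** In sections 6.6.1 and 6.17, define the analysed knowledge outcome as the number of correct answers, 0 to 9, for each woman and each husband. Compare it between arms in the GEE already planned in section 6.24, adjusted for the respondent's baseline score. Keep the share reaching 75% as a supporting summary, stated as 7 or more of 9 so that the word about leaves no doubt over 6 of 9.

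The cost is about two sentences and no extra data. An answer key for each form is needed, because item 608 in the women's English form and item 208 in the husbands' ask different things. The downside is that the headline becomes a mean difference in items correct, which is less immediate than a percentage; the supporting summary covers that.
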